#### Evaluation phase

This phase will assess the effectiveness of training program and the incidence of the DD among children born to mothers who participated in the training program. Mothers will have to undergo at least 2 of the three educational/training sessions.

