## Hypothesis

Mothers in the Intervention group can identify the early red flag signs of developmental disorders more easily than the control group.

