#### Implementation phase

This Phase of the study employs a non-randomized intervention design to assess the impact of a targeted multimethod parental educational intervention on antenatal mothers. This phase seeks to provide valuable insights into the practical application and potential benefits of the neuro parenting program. A comparison is made between the intervention group, exposed to the neuro parenting program, and a control group receiving routine care without training sessions. The primary outcomes center around evaluating the percentage of mothers who suspect early childhood developmental disorders including true positive, false positive and false negative ratio. The confirmation of DD will be done using Bayley Scale for Infant Development IV. The study entails a meticulously structured follow-up period, with strategically defined time points to assess the program’s efficacy across critical stages of early development. Assessments will be conducted at birth, six months, and twelve months postpartum to monitor developmental trajectories. By demarcating these specific follow-up intervals, the study ensures a systematic framework for evaluating intervention outcomes, particularly the capacity of mothers to recognize neurodevelopmental indicators and suspect potential developmental disorders. This follow-up design is structured to capture the program’s lasting influence on maternal awareness and accuracy in identifying developmental milestones, offering a precise evaluation of the intervention’s long-term impact. Through targeted assessments, the study will measure both immediate and long-term effects on maternal ability to recognize early developmental cues, providing a focused understanding of the intervention’s effectiveness. Implementation strategies are illustrated in Fig. 1 and the timeline has been depicted in Table 1.

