**Fig. 1 Fig1:**
[figure not shown]
Implementation strategy

**Table 1 Tab1:** Spirit time line

	Enrollment and Allocation					Post Allocation				Endline evaluation		Close Out	
**TIME POINTS**	-t4	-t3	-t2	-t1	t0	t1	t2	t3	t4	t5	t6	t7	t8
Team building	X	X											
Stake holder consultations and ethical proceedings	X	X											
Development of BCC Material			X	X									
Evaluation of BCC			X	X									
Preparation of questionnaire for baseline evaluation			X	X									
Baseline survey of knowledge of antenatal mothers					X								
Recruitment					X	X	X	X	X				
Training to antenatal women in intervention group (2 sessions)						X	X	X	X	X	X		
3rd training session – In postnatal period to intervention group								X	X	X	X		
Evaluation of training						X	X	X	X	X	X		
Interview with control mothers								X	X	X	X		
Endline evaluation of intervention								X	X	X	X		
Data analysis												X	X
Report writing												X	X

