##### Intervention

Antenatal women with willingness to participate will be enrolled in the study after obtaining Informed Consent. The antenatal mothers who visit the hospital for antenatal care will be explained about the online module regarding its uses and accessibility of the information. In addition, they will be provided information regarding observing the growth and activities of the child. For the control group, antenatal mothers enrolled as controls, regular check ups as per the standard protocol and the printed material for identification of neurodevelopmental signs will be provided. The intervention comprises three strategically timed training sessions during the second trimester, third trimester and postnatal care, specifically targeting mothers of preterm babies.

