### Survey on neurodevelopmental outcomes

Targeting mothers who have attended parental educational interventions, a cross-sectional study will be employed to assess the percentage of mothers suspected of early childhood developmental disorders as a result of the training received.

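### The evaluation sections are written around mothers who attended training, in conflict with the planned comparison of the two groups

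*Protocol article*

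**What the plan says.** All references are to the protocol article. Some sections set up a comparison of two groups:

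- Hypothesis: intervention mothers will identify red flags "more easily than the control group".
- Implementation phase: "A comparison is made between the intervention group, exposed to the neuro parenting program, and a control group receiving routine care without training sessions". Its primary outcome is described as "evaluating the percentage of mothers who suspect early childhood developmental disorders", together with true positive, false positive and false negative results. Assessments are at birth, 6 months and 12 months.
- Table 1 has a row "Interview with control mothers" at t3 to t6, the same columns as the endline evaluation.
- Training and assessment refers to assessing every participant.

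Other sections describe evaluation in trained mothers:

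- Evaluation phase: the phase will assess "the incidence of the DD among children born to mothers who participated in the training program", and then "Mothers will have to undergo at least 2 of the three educational/training sessions".
- Survey on neurodevelopmental outcomes: "Targeting mothers who have attended parental educational interventions, a cross-sectional study will be employed". The percentage it measures is loosely worded but appears to be the one named as primary outcome.

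The Intervention section spreads the three sessions from the second trimester to the postnatal period. The article does not say how mothers with no session or one session are handled.

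**The concern.** A mother meets or fails a two-session condition only after enrolment. Controls have no sessions, so no matching condition can be applied to them. If the condition decides who is evaluated, the more engaged part of one arm is compared with the whole of the other. Engagement plausibly goes with a greater readiness to notice and report a developmental concern, which is the outcome. Part of any observed difference could then come from who was kept rather than from what was taught. Allocation is already non-randomised, so this would be a second source of selection, and an avoidable one.

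The survey raises a different problem. Measured in attenders only, a percentage has no comparator and cannot show that training made a difference. The two problems belong to different readings (attenders against controls, or no comparison at all) and do not apply to the same analysis.

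**Working it through.** **1. The planning inputs.** The Sample size section gives 5%, an odds ratio of 2, 80% power, 95% confidence, 20% dropout and 513 per group, rounded to 520. The 5% is described as an exposure rate; using it as the control proportion is an assumption.

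- Intervention proportion: p1 = 2 × 0.05 / (0.95 + 2 × 0.05) = 0.0952.
- Two-sided, unpooled variance: n = (1.960 + 0.842)² × (0.05 × 0.95 + 0.0952 × 0.9048) / (0.0452)² = 512.7, so 513.

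This reproduces 513, but as the number before dropout (a separate point). With 20% dropout, 520 × 0.8 = 416 completers per arm, and power at an odds ratio of 2 is 71%.

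**2. Selection with no training effect.** The article gives no attendance figure. Assume that a share a of 60% to 90% attends at least two sessions, that attenders have s = 1.5 to 3 times the odds of suspecting a disorder that non-attenders have, and that the whole arm has a rate of 5%, as in controls. With q the rate in non-attenders and pA = s·q / (1 − q + s·q), solve a·pA + (1 − a)·q = 0.05. The apparent odds ratio is [pA / (1 − pA)] / [0.05 / 0.95].

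Example, a = 0.8 and s = 2: q = 0.0285, pA = 0.0554, apparent odds ratio = (0.0554 / 0.9446) / 0.0526 = 1.11.

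Apparent odds ratio, with the false-positive rate of a two-sided 5% test in brackets (416 controls, 416·a attenders):

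| Attendance | s = 1.5 | s = 2 | s = 3 |
|---|---|---|---|
| 90% | 1.04 (5.1%) | 1.05 (5.3%) | 1.07 (5.6%) |
| 80% | 1.07 (5.6%) | 1.11 (6.4%) | 1.16 (7.6%) |
| 70% | 1.11 (6.3%) | 1.18 (8.2%) | 1.26 (11.2%) |
| 60% | 1.16 (7.3%) | 1.26 (10.8%) | 1.38 (16.7%) |

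A second parameterisation agrees. If a share f of low attenders detects at r times the attenders' rate, pA = 0.05 / [(1 − f) + f·r]. The odds ratio is 1.12 for f = 0.2, r = 0.5; 1.19 for f = 0.3, r = 0.5; and 1.31 for f = 0.3, r = 0.25.

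**3. What including everyone costs.** Assume that attenders have an odds ratio of 2 and non-attenders gain nothing. The arm's rate is p = a × 0.0952 + (1 − a) × 0.05. At a = 0.8, p = 0.0862 and the odds ratio is (0.0862 / 0.9138) / 0.0526 = 1.79.

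| Attendance | Odds ratio, all enrolled | Power at 416 per arm | Needed per arm before dropout (pooled formula) |
|---|---|---|---|
| 100% | 2.00 | 71% | 516 |
| 90% | 1.90 | 63% | 619 |
| 80% | 1.79 | 55% | 760 |
| 70% | 1.69 | 45% | 962 |
| 60% | 1.59 | 36% | 1268 |

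**The case against.** The strongest reply is that the two-session sentence is not an analysis-set rule. It can be read as what the programme asks of its participants, and nothing in it says that mothers with fewer sessions leave the comparison. Analysis sets are commonly left to a full protocol or SAP, and neither is shown. This stands, and it makes the selection argument conditional. It does not remove the conflict: the sentence follows one that limits the assessment of developmental delay to children of trained mothers, and the survey's restriction to attenders is explicit.

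A reader might infer that the trial has no control comparison. The documents do not support that. The Implementation phase section plans one, Table 1 schedules control interviews, and the survey may be an extra study in trained mothers. The reference to every participant under Training and assessment is weaker support, because that questionnaire follows completion of the training module.

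A reader might also infer that the controls are unselected. They are unselected on attendance only: they consent, commit to follow-up visits and face the same exclusion for difficulty with follow-up.

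Finally, the Intervention section's wording, "during the second trimester, third trimester and postnatal care, specifically targeting mothers of preterm babies", might be taken as a second filter on who is evaluated. It describes whom the sessions target, possibly only the postnatal one, and Table 1 gives the third session to the intervention group as a whole. A mother who misses the third-trimester session can still reach two through the other two. The most that follows is that the phrase needs reconciling with Methodology and Eligibility criteria, which describe antenatal mothers from the second trimester.

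It is also fair to say that the magnitudes are assumed and well short of an odds ratio of 2, and that analysis by assigned group does not give a non-randomised study the protection it gives a randomised one.

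**Conclusion.** The point holds in a limited form. The article contradicts itself on who is evaluated, and this is a conflict in stated text rather than a detail left out. The survey of attenders cannot on its own test the hypothesis, and that conclusion needs no figures.

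The selection effect depends on the two-session condition being used to decide who is analysed. In that case the apparent odds ratio with no true effect is about 1.04 to 1.38, and the false-positive rate 5.1% to 16.7% instead of 5%. Both ranges rest on assumed attendance, an assumed difference between attenders and non-attenders in the direction of more suspicion, and 5% taken as the outcome rate. The effect would come on top of whatever imbalance non-random allocation brings.

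**What to change.** - In Evaluation phase, state that the primary comparison includes all enrolled mothers in their assigned group, whatever sessions they attended. Keep attendance of at least two of the three sessions as a supportive analysis, and say how mothers with no session or one session are handled.
- In Survey on neurodevelopmental outcomes, apply the survey to both arms with the same form at the 6- and 12-month assessments already planned.
- Reconcile the preterm wording in Intervention with Methodology and Eligibility criteria.

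The change is mainly wording. Table 1 already schedules control interviews alongside the endline evaluation, though the control interview may need the survey's items added. The real cost is dilution. If non-attenders gain nothing, 80% attendance turns an odds ratio of 2 into about 1.79 and leaves about 55% power at 416 per arm, against 71% with full attendance. The sponsor should acknowledge this and state the attendance it expects. The loss of power is not a reason to exclude non-attenders from the primary comparison.

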### Training and assessment

In this phase, all participants will undergo a thorough assessment of training outcomes. The implementation strategy involves providing participants with a comprehensive questionnaire covering knowledge, awareness, and practices related to identifying early child development delays based on the training module. This questionnaire will be administered after the completion of the training module. Upon concluding all training sessions, a final questionnaire will be developed to gauge participants’ overall knowledge, practice, and understanding of the training’s importance. Descriptive statistics will be calculated to analyse quantitative variables, providing insights into the numerical aspects of the participants’ responses. For quantitative variables, frequencies and percentages will be computed, offering a quantitative overview of the participants’ understanding and practices. To explore the association between variables, the chi-square test will be employed, with a significance level set at 5%.

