#### Secondary objectives

To determine the yield of early detection by parents of early red flag signs of childhood developmental disorders.To estimate the level of improvement of knowledge in early red flag signs of childhood development disorders among the parents.

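### Women recruited after t0 have no scheduled baseline knowledge score, and nothing puts the before and after questionnaires on one scale

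*Protocol article*

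**What the plan says.** - **Objective.** The second of the Secondary objectives is: "To estimate the level of improvement of knowledge in early red flag signs of childhood development disorders among the parents". This is a change, so it needs a value before training and a value after it.
- **Baseline.** In Table 1 the row "Baseline survey of knowledge of antenatal mothers" has one mark, in t0. A questionnaire for that survey is prepared in -t2 and -t1.
- **Recruitment.** The recruitment row of Table 1 is marked in five columns, t0 to t4.
- **Training.** The row "Training to antenatal women in intervention group (2 sessions)" is marked t1 to t6, and the row "3rd training session – In postnatal period to intervention group" is marked t3 to t6.
- **Later measurement.** Control interviews and endline evaluation are both marked t3 to t6. Columns t7 and t8 hold only analysis and reporting.
- **Later instruments.** Training and assessment describes a questionnaire built on the training module and says: "This questionnaire will be administered after the completion of the training module". It continues: "Upon concluding all training sessions, a final questionnaire will be developed". The same section says that everyone in the study is assessed.
- **Follow-up.** Implementation phase says: "Assessments will be conducted at birth, six months, and twelve months postpartum".
- **Design.** Allocation is not randomized, and 520 women are planned per arm.

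**The concern.** If Table 1 is followed as printed, a woman recruited in t1 or later enters, and may be trained, without a knowledge score on record. That score cannot be collected afterwards. For women who do have a baseline, the article does not say that the later questionnaires repeat it, so a difference between two scores could reflect a harder or easier form as well as learning.

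The design makes this more serious. With randomization, a comparison of scores after training would stand without a baseline. Here the intervention arm consists of women willing to join the parenting program. If they already knew more, or were more motivated to learn, a comparison based only on later scores would credit that to the training.

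A related scheduling question is whether the endline window is long enough for the 12-month assessment of late enrolees. It bears mainly on the primary detection outcome, but it arises from the same table and is settled by the same revision.

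**Working it through.** The plan gives no figure for this point, so there is none to reproduce. The check reads Table 1 by column and sets it beside the text.

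**1. Is t0 calendar time or each woman's own entry?** The same axis carries team building (-t4, -t3), development of materials (-t2, -t1) and recruitment over five columns. These are project activities, and recruitment in t1 to t4 has no meaning if t0 is the moment each woman enters. Calendar time is the natural reading.

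**2. Who has a baseline on that reading?** One of the five recruitment columns carries the survey. Planned total: 2 × 520 = 1040. If accrual were even over the five columns (an assumption; the article gives no accrual pattern):
- with a scheduled baseline: 1040 × 1/5 = 208
- without one: 1040 × 4/5 = 832 (80%)

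**3. Are the measurements on one scale?** Three forms appear.

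| Form | When | Link to baseline stated? |
|---|---|---|
| Baseline questionnaire | prepared -t2 and -t1, used in t0 | not applicable |
| Post-training questionnaire | after the module | none |
| Final questionnaire | to be developed after all sessions | none; as worded, it does not exist at t0 |

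For controls, who have no module to complete, the trigger for the second form is undefined, although the text includes them in the assessment.

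**4. Does the endline window reach 12 months postpartum?** Assumptions: entry at gestational weeks 14 to 27 and delivery at week 40 (the article says only that entry is from the second trimester), with 30.44 days per month.

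Months needed = (40 − week) × 7 / 30.44 + 12
- week 14: 26 × 7 / 30.44 + 12 = 18.0
- week 27: 13 × 7 / 30.44 + 12 = 15.0

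Endline closes at the end of t6. Minimum column length:
- enrolled at the end of t4 (two columns left): 15.0/2 to 18.0/2 = 7.5 to 9.0 months
- enrolled at the start of t4 (three columns left): 15.0/3 to 18.0/3 = 5.0 to 6.0 months

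| Column length | Time from t4 enrolment to end of t6 | 12 months postpartum reached? |
|---|---|---|
| 3 months | 6 to 9 months | by no t4 enrolee |
| 6 months | 12 to 18 months | by early t4 enrolees only |
| 9 months | 18 to 27 months | by all |

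**5. Does Table 1 hint at the column length?** The postnatal session first appears in t3. With columns of L months, a woman who enters at the end of t0 in week 14 delivers at about month L + 6, and t3 opens at month 3L. The gap is 3L − (L + 6) = 2L − 6 months: 0 at L = 3, 6 at L = 6, 12 at L = 9. Columns long enough for the last enrolee's 12-month visit therefore fit poorly with the postnatal row. This suggests shorter columns but does not establish them.

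**The case against.** Several points on the other side are fair.

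- **The objective is not out of reach altogether.** A reader might infer that improvement cannot be estimated at all. The article does not support that. Women enrolled in t0 have a baseline, and because everyone is to be assessed, the arms can be compared after training. What is lost is the within-mother gain for most enrolees and the protection that a baseline gives against prior differences.
- **Controls are not shown to be left out.** A reader might infer that they can show no parallel change. The baseline row is not limited to the intervention arm, unlike the training rows, and the control interviews fall in the same columns as endline. Controls also receive printed material on neurodevelopmental signs, so a knowledge form is meaningful for them.
- **Not every later form is shown to be new.** The article does not say that the first post-training form differs from the baseline form. Even the wording on the final form may be loose, since Evaluation of program effectiveness describes it as given, not developed, at the end of training. Item content is commonly left to the full protocol. It remains true that no passage names one instrument used before and after.
- **The table may mix two clocks.** It sets t0 under enrolment and t1 onward under post-allocation. If t0 were each woman's own entry, nobody would lack a baseline. The set-up and recruitment rows make this the weaker reading, but the table leaves it open.
- **The 12-month shortfall is conditional.** A reader might infer that late enrolees certainly miss that visit. Column length is not stated, and entry after the second trimester is not clearly excluded, which would shorten the interval.

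**Conclusion.** The point holds in this form. On the calendar reading of Table 1, women recruited in t1 to t4 have no scheduled pre-training knowledge score, and the text does not place the before and after measurements on a common scale. As scheduled, improvement in knowledge cannot be estimated within mothers for most enrolees. The comparison of arms that remains would be confounded by any difference in prior knowledge.

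The size, about four in five women, rests on even accrual and on the calendar reading. The 12-month matter is a request to reconcile and not a demonstrated loss: the endline window suffices for women enrolled at the end of t4 only if columns last about 7.5 to 9 months, given entry at weeks 14 to 27.

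The objective affected is secondary, but the gap should be closed before recruitment starts because a missed baseline cannot be recovered.

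**What to change.** 1. Use one knowledge questionnaire, finalised before recruitment opens. Give it in both arms at each woman's enrolment (t0 to t4, before any training) and again at endline.
2. Compare arms on the endline score adjusted for the baseline score. Details of the model can stay in the statistical analysis plan. The adjustment deals with measured prior knowledge, not with every difference between non-randomized arms.
3. Correct the baseline row of Table 1 so that it spans the same columns as recruitment, and word Training and assessment so that the later form is the baseline form repeated. Extra items on the module can be added and reported separately.
4. State the length of each column in Table 1 and reconcile it with the 12-month assessment. If columns are shorter than about 7.5 to 9 months, either move the start of analysis or close recruitment earlier.

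Cost: a short form at each enrolment, a revised table, and possibly some added calendar time or a shorter recruitment window.

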### Evaluation of program effectiveness

At the end of all training sessions, a final questionnaire will assess how much knowledge, practical skill, and understanding participants gained from the program. It will focus on instances where mothers correctly identify developmental concerns, which are then confirmed by healthcare professionals. This evaluation will systematically measure the program’s effectiveness in equipping mothers with the ability to identify developmental disorders with precision. Beyond these direct impacts, the assessment will adopt a holistic approach, evaluating the intervention’s broader influence on multiple domains, including communication, learning, and behavioural development, to provide an in-depth understanding of its effectiveness in supporting comprehensive neurodevelopmental health.

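### The plan has the final knowledge and effectiveness questionnaire developed only after training has ended; it should be fixed before the first training session

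*Protocol article*

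**What the plan says.** Three places in the protocol article bear on this instrument.

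- **Training and assessment.** A first questionnaire on knowledge, awareness and practices is administered once the training module is complete. The next sentence turns to a second instrument: "Upon concluding all training sessions, a final questionnaire will be developed".
- **Evaluation of program effectiveness.** Here the same instrument is described as in use: "At the end of all training sessions, a final questionnaire will assess how much knowledge, practical skill, and understanding participants gained from the program". The section adds: "It will focus on instances where mothers correctly identify developmental concerns, which are then confirmed by healthcare professionals".
- **Table 1.** The two antenatal sessions are marked t1 to t6. The row "3rd training session – In postnatal period to intervention group" is marked t3 to t6, and so is the row "Endline evaluation of intervention". The only row for preparing a questionnaire is "Preparation of questionnaire for baseline evaluation", at -t2 and -t1.

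The secondary objectives include estimating how far parents' knowledge improves, and the abstract says that outcomes are assessed through questionnaires.

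**The concern.** The only statement of when the final questionnaire is created puts that step after training. Elsewhere the questionnaire is in use at that same point, and the timeline has endline evaluations under way while training continues. Two things could go wrong.

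1. Mothers evaluated before the instrument exists would have no value on it.
2. An instrument written after training has been delivered, and after an earlier questionnaire has been answered, can be shaped by what was taught and by responses already seen. The study is non-randomized and controls receive no training sessions, so the team can know which mothers were trained.

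There is also a measurement issue. Improvement in knowledge needs comparable measures before and after. The baseline questionnaire is prepared before recruitment and the final one at some later time, with no stated link between them.

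**Working it through.** The plan gives no figure for this point, so the check sets the passages against the timeline.

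**Step 1: read Table 1 by column position (13 columns, -t4 to t8).**

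| Row | Columns marked |
|---|---|
| Baseline questionnaire preparation | -t2, -t1 |
| Recruitment | t0 to t4 |
| Antenatal training, two sessions | t1 to t6 |
| Third (postnatal) session | t3 to t6 |
| Endline evaluation | t3 to t6 |

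Endline overlaps training in all four of its periods, and three of them (t3, t4, t5) come before the last training period. The column-group header for endline covers only t5 and t6. Taking the header instead of the row narrows the overlap but leaves it in place.

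**Step 2: programme-wide reading.** If the questionnaire is created after the last session of the whole programme, no endline evaluation in t3 to t5 can use it. The share affected depends on how endline evaluations are spread over t3 to t6, which the article does not give. Share before t6 = 1 − (weight at t6) / (sum of weights):

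| Assumed weights t3:t4:t5:t6 | Share before t6 |
|---|---|
| 1:1:1:1 | 1 − 1/4 = 75% |
| 1:2:3:4 | 1 − 4/10 = 60% |
| 4:3:2:1 | 1 − 1/10 = 90% |
| 1:1:1:3 | 1 − 3/6 = 50% |
| 1:1:1:5 | 1 − 5/8 = 37.5% |

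With 520 mothers per arm, even spread would mean 0.75 × 520 = 390. The other patterns run from 0.375 × 520 = 195 to 0.90 × 520 = 468. All of these are assumptions, and they also suppose that controls follow the same pattern.

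**Step 3: per-mother reading.** Each mother's own sessions end at different calendar times because recruitment is staggered. The overlap in Table 1 is then ordinary and no timing conflict remains. What remains is the order of events: training delivered, first questionnaire answered, final questionnaire developed.

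**Step 4: what a shift in the instrument could do (illustration only).** Take 520 × 0.80 = 416 completers per arm, a two-sided 5% test of two proportions, and no true difference. Suppose that the choice of items raises the trained arm's pass rate from 50%. By the normal approximation, power = Φ[(d − 1.96 × SE pooled) / SE unpooled].

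- 50% vs 60%: SE pooled = √(2 × 0.55 × 0.45 / 416) = 0.0345; SE unpooled = √((0.25 + 0.24) / 416) = 0.0343; Φ[(0.10 − 0.0676) / 0.0343] ≈ Φ(0.94) ≈ 0.83.
- 50% vs 55%: SE pooled = 0.0346; SE unpooled = 0.0346; Φ[(0.05 − 0.0679) / 0.0346] ≈ Φ(−0.52) ≈ 0.30.

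The 50% pass rate and both shifts are assumed. The figures show that at this sample size a modest artefact would often reach significance. They do not show that late drafting produces such a shift.

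**The case against.** The strongest reply is that the verb in Training and assessment is loose wording for giving the questionnaire. The program-effectiveness section has it assessing gains at the same moment, and the Intervention and Evaluation phase sections describe three sessions of which each mother attends at least two, which favours the per-mother reading. This may well be what was meant. But consecutive sentences in Training and assessment use one verb for administering the first questionnaire and another for developing the final one, so a reader cannot treat them as equivalent. If it is a slip, the correction is one sentence.

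A reader might go further and infer that most mothers reach endline before their outcome instrument exists. The documents do not support that. It requires the programme-wide reading and an accrual pattern that is not given. It also overstates the instrument's role. The Implementation phase defines the primary outcome by mothers' suspicion of a disorder, with confirmation on the Bayley scale. Interim and follow-up describes a separate brief questionnaire on red flags and determines true positives by comparing parents' evaluations with professionals'. None of these waits for the final questionnaire. The program-effectiveness section links it to confirmed identifications, but does not make it their only source.

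Two further points stand in part. The absence of a Table 1 row is weak evidence alone, since an article condenses the full protocol; it counts only because the text that is present states a timing. And freezing the instrument early would not stop it from using taught wording, since the post-training questionnaire is based on the module by design. It would stop the content from being adapted to training as delivered or to answers already seen.

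**Conclusion.** The point holds in a limited form. As written, the final knowledge and effectiveness questionnaire is created after training, and the two sections and Table 1 do not agree on when it exists. On the programme-wide reading, some mothers could not be scored on it; the assumed patterns give about 38% to 90%, and no figure within or outside that range can be derived from the article. On the per-mother reading, nobody is left unscored, but the instrument is still not fixed until training has been delivered and earlier responses collected. Either way, the exposure is to the secondary objective on knowledge improvement and to the program-effectiveness assessment. An effect on the primary outcome is not shown. The size of any bias is unknown; the 30% and 83% figures illustrate the risk under assumed shifts and do not measure it.

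**What to change.** In Training and assessment, replace the sentence on the final questionnaire with a statement that:

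- the final questionnaire and its scoring key are developed, validated and frozen in the preparatory phase (-t2, -t1), alongside the baseline questionnaire so that change can be measured, and before the first training session at t1;
- the frozen version is administered unchanged after each mother's last session, and at matching times in controls, who have no sessions to anchor it.

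Align Evaluation of program effectiveness with this wording and add a preparation row for the endline instrument to Table 1.

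This moves an existing task earlier and needs no extra participants or visits. The downside is that items thought of later cannot enter the confirmatory instrument.
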